#### Secondary outcomes

**Patients**

*Outpatient contacts*, grouped into:*Ascites contact*: outpatient visits or short admissions in which paracentesis is the sole intervention.*Planned and unplanned clinical visits* in the outpatient clinic.*Planned and unplanned telephone calls* either initiated by or directed to the patient.*Change in symptom burden*, will be assessed using the 24-item PRO-Pall questionnaire [31]. The questionnaire was developed from the 15-item EORTC QLQ-C15-PAL together with nine additional items recommended by the Danish Health Authorities. The questionnaire will be administered at baseline and prior to each planned visit.*Change in quality of life*, assessed using the EQ-5D-5 L instrument at baseline and prior to each planned study visit [36].

**Caregivers**

*Change in caregiver burden*, measured using the 22-item Zarit Burden Interview (ZBI) at baseline and before each planned study visit [37].

**Health care professionals**

*Change in experience of burnout*, measured using the Copenhagen Burnout Inventory (CBI) before intervention start and one year into Phase 3 [38].

**Health economic outcomes**

*Cost-effectiveness analysis*, based on the number and length of hospital admissions per patient during the follow-up period.*Cost-utility analysis*, assessing the cost per Quality-Adjusted Life Year (QALY) based on the results of EQ-5D-5 L data.

### Implementation outcomes

An overview of the process indicators and methods of measurement for the feasibility study and process evaluation are presented in Table 1.

**Table 1 Tab1:** Overview of process indicators and methods of measurement and data collection

Domain	Method	Process indicators	Data sources
Reach and uptake	Descriptive quantitative evaluation	Number of patients referred for the intervention Number of patients included of all eligible Referral patterns	Screening data
Effectiveness	Preliminary quantitative evaluation of endpoints in Phase 2 and quantitative evaluation of endpoints in Phase 3 Cost-effectiveness analysis Cost-utility analysis	Number and length of hospital admissions Patient reported outcomes Change in caregiver burden Staff time, training, materials Healthcare utilization QALYs gained	Medical records PRO-Pall EQ-5D-5 L ZBI Danish DRG tariffs EQ-5D-5 L
Adoption		Proportion of sites offering the intervention	Information from study sites
		Differences in implementation between implementation sites	
*Implementation:* Feasibility: *The degree to which the intervention can be carried out in a given setting.*	Mixed-method evaluation Descriptive quantitative evaluation Qualitative evaluation	Resource utilisation Palliative care planning processes No. of invitation leaflets handed out to participants and families No. of palliative conversations per participant No. of informal caregivers participating in palliative conversations. No. of PRO-Pall questionnaires completed for each palliative conversation. No. of medical interventions. No. of patients referred to palliative care teams No. of patients referred to hospices No. of patients referred to municipal offers (exercise, nutrition, alcohol treatment, etc.) Patient experience Caregiver experience Healthcare personnel experience	Self-developed questionnaire with open-ended questions on experiences with palliative care, pre-study training, and the intervention
*Fidelity: The degree to which the intervention was implemented as intended.*			Informal conversations with health care professionals
Acceptability and Appropriateness: *The perception among implementation stakeholders that a given intervention is agreeable*,* palatable*,* or satisfactory.*			Semi-structured interviews informal caregivers and patients
			Medical records
			Semi-structured qualitative interviews
Maintenance	Qualitative and quantitative evaluation	Measures on Reach, effectiveness, after 12 months, two years, three years and five years.	

The feasibility study, Phase 2, explores the acceptability and implementation of the palliative care intervention. Using a mixed-method design and the RE-AIM Framework, the study assesses reach, uptake, fidelity, and preliminary patient and caregiver outcomes across the departments.

Qualitative interviews with patients, informal caregiver, and healthcare professionals will be conducted to assess the intervention’s acceptability and appropriateness. Two subgroups of approx. 20 patients and 20 informal caregivers (five from each study center) will be interviewed to explore their experiences with the intervention. Study nurses and hepatologists involved in delivering the palliative care intervention will be interviewed to assess their perspectives on its implementation and impact as part of Phase 3, the intervention study.

## Sample size and statistical methods

### Sample size

The study aims to include 240 patients and 100 informal caregivers, based on sample size calculations for the most significant outcomes and to accommodate expected attrition.

The Healthcare System Burden will be measured as the number and length of admissions. Patients with cirrhosis spend an average of seven days per year in hospital [39]. Health care utilization data from the intervention group will be compared to a recent historical cirrhosis cohort. For the sample size calculation, we assumed the historical cohort will have an average of seven days in hospital per year and hypothesize that the intervention will cause a reduction of two days/year with an assumed SD of 7 days. Hence, 199 participants are required (STATA BE 18.5). With an estimated attrition rate of 20%, we aim to include 240 patients [40, 41].

Caregiver burden will be measured using the 22-item ZBI (range 0–88). A change of 5 points is considered realistic and clinically relevant. Based on previous studies, this change can be detected with 100 informal caregivers if the standard deviation (SD) of the change is around 14 [35, 36].

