**Methods:**

The LiverCare study is a multi-center, mixed-method, pragmatic, non-randomised clinical study with a hybrid type 1 effectiveness-implementation design. The study is conducted in hepatology departments across four hospitals in three of Denmark’s five regions. It is guided by the British Medical Research Council and Reach, Effectiveness, Adaption, Implementation, Monitor frameworks and includes both a feasibility study and a mixed-method process evaluation.

The LiverCare intervention is grounded in a palliative approach, emphasising open, exploratory palliative care conversations. The intervention is integrated into routine outpatient care and the palliative care conversations are delivered by hepatologists and liver nurses who attended a specially designed course within palliative care. Eligible participants are adults with decompensated liver cirrhosis of any etiology who meet at least one general and one disease-specific palliative care indicator, assessed using the Supportive and Palliative Care Indicators Tool. Informal caregivers are invited to participate in the intervention.

Palliative care conversations are initiated following a formal invitation and continue after four to ten weeks and then every six months up to 36 months or until study withdrawal or death. The primary outcome is healthcare utilization, defined as the number and length of hospital admissions, compared to a historic cohort. Secondary outcomes include outpatient contacts, symptom burden, quality of life, and caregiver burden. The study also includes cost-effectiveness and cost-utility analysis.

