### Participants and eligibility criteria

#### Inclusion criteria for patients are as follows

Adult patients with the diagnosis of cirrhosis of any etiology (clinically, radiologically, or histologically confirmed) as the predominant chronic illness.At least one general and one disease-specific palliative care indicator assessed by the Supportive and Palliative Care Indicators Tool (SPICT).Ability to provide informed consent.Ability to read and understand Danish.

SPICT is a needs-assessment clinical tool developed to identify individuals with serious or advanced illness who are at risk of deteriorating health or dying and who may benefit from palliative care [26]. It supports healthcare professionals in recognising potential unmet palliative needs by combining general and disease-specific indicators, although it does not itself determine the exact nature or severity of those needs. In this study, patients were eligible for inclusion if they had at least one general and one disease-specific SPICT indicator.

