#### Exclusion criteria include

Inability to provide informed consent or comply with the study protocol.Diagnosis of advanced malignant disease other than hepatocellular carcinoma.Current contact with specialised palliative care services or hospice.Being listed for liver transplantation.

Eligible patients are invited to participate by a hepatologist or specialised liver nurse, either during hospitalisation or at an outpatient visit. Participation is voluntary, and patients are informed that they may withdraw consent at any time. Patients are encouraged to nominate an informal caregiver to participate in the study. Informal caregivers can include family, close friends, or any other person chosen by the patient. To be eligible, the informal caregiver must be at least 18 years old, be able to speak and understand Danish, and available to participate in at least one study visit. After receiving oral and written information, patients are given at least 24 h to consider participation. If the patient agrees, the first study appointment is scheduled.

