### Intervention elements

The intervention is delivered alongside standard care and integrated into patients’ regular clinical appointments. In all participating settings, standard care involves routine follow-up of patients with cirrhosis by a team of hepatologists and specialised liver nurses. Following an admission due to decompensated cirrhosis, patients are routinely offered planned follow-up in an outpatient clinic.

The initial palliative care conversation is conducted by a hepatologist in collaboration with a specialised liver nurse. Alternatively, the conversation may be conducted solely by the liver nurse. Subsequent conversations are conducted by either a hepatologist or a liver nurse after 4–10 weeks, and at 6, 12, 18, 24, 30, and 36 months, or until withdrawal from the study or death. Extra visits may be scheduled if clinically indicated or if the patient or informal caregivers request additional support or planning.

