### Effectiveness outcomes

#### Primary outcome

*Healthcare system burden*, measured as the number and length of hospital admissions from the initial visit to death or study exit. Data on health care utilisation will be prospectively recorded by registering events since the last visit at each study visit and compared to a recent historic cohort of a similar size from the involved centers.

Hospital admissions will be categorised into three mutually exclusive groups:

*Liver-related admissions*: inpatient stays of ≥ 24 h due to complications of liver cirrhosis, including variceal bleeding and other bleeding related to portal hypertension, hepatic encephalopathy, spontaneous bacterial peritonitis, hepatorenal syndrome, alcoholic hepatitis, ascites, infection, electrolyte imbalances, increasing frailty, sarcopenia, or poor nutritional status.*Non-liver-related admissions*: inpatient stays of ≥ 24 h for conditions not directly related to cirrhosis.*Short admissions*: hospital stays of < 24 h, excluding admissions in which paracentesis is the sole intervention.

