### Statistical methods

All data will be entered into a shared REDCap database [42]. Descriptive statistics for numerical data will be presented as means with standard deviations (SD) for normally distributed variables, or as medians with interquartile ranges (IQR) for non-normally distributed variables. Categorical data will be presented as counts and proportions. For between-group comparisons, unpaired two-sample Student’s *t*-tests will be used for normally distributed numerical data, and the Wilcoxon-Mann-Whitney test for non-normally distributed numerical data. Categorical variables will be compared using the chi-squared test. Differences between groups will be reported as means with standard errors (SE) and 95% confidence intervals (CI) for numerical outcomes, and as odds ratios (OR) with 95% CI for dichotomous outcomes. All statistical analyses will be conducted using Stata Statistical Software, version 16 (StataCorp, College Station, Texas). Missing data will be reported and explored. Where appropriate, multiple imputation techniques will be considered. Both intention-to-treat (ITT) and per-protocol analyses will be conducted to assess robustness of findings.

The cost-effectiveness analysis will include cost and effect. The costs will include intervention-related expenses (e.g. staff time, training, materials) while the effect will include the use of healthcare resources using Danish DRG standard tariffs.

The cost-utility analysis will be based on the EQ-5D-5 L-data and the values will be converted to utility scores using Danish population-based value [43]. These scores will be used to estimate QALYs, which will serve as the measure of effectiveness.

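### The primary outcome is compared with a historic cohort that cannot follow the trial's start rule, and the trial's own population is defined in two ways, so the groups may differ in disease stage and starting point

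*Protocol article*

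**What the plan says.** **Comparator.** The Primary outcome section says utilisation is "compared to a recent historic cohort of a similar size from the involved centers". The Sample size section says "Health care utilization data from the intervention group will be compared to a recent historical cirrhosis cohort". Together these fix recency, approximate size, centres and a diagnosis of cirrhosis. Neither gives eligibility criteria or an index date for the historic patients.

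**Start of counting.** In the Primary outcome section, admissions are counted "from the initial visit to death or study exit". Under the exclusion criteria, patients are invited "either during hospitalisation or at an outpatient visit". They then have at least 24 hours to decide, and the first study appointment is booked if they agree.

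**Trial population.** The abstract's Methods paragraph says "Eligible participants are adults with decompensated liver cirrhosis of any etiology". The inclusion list begins "Adult patients with the diagnosis of cirrhosis of any etiology" and adds SPICT indicators (one general, one disease-specific), capacity to consent and a Danish-language requirement. Decompensation is not on that list. The exclusions remove transplant-listed patients, those already in specialised palliative care or hospice, and those with advanced malignancy other than hepatocellular carcinoma.

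**Analysis.** For between-group comparisons, the Statistical methods section names the unpaired t-test, the Wilcoxon-Mann-Whitney test and the chi-squared test. None of these adjusts for covariates.

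**The concern.** With a historic control, a difference in hospital days can be read as an effect of the intervention only if both groups were selected alike and followed from a comparable moment. The plan as written does not secure either condition.

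The intervention group has passed several filters (SPICT, consent, exclusions, attendance at a first visit) before its clock starts. No counterpart is stated for the comparator, and its patients never had the visit that defines time zero. Someone extracting the historic data would have to choose another starting date, and the result could depend on that choice.

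The two population statements make this worse, because it is unclear which population the comparator should match. Stage matters a great deal by the document's own account. The Introduction puts median survival at about 12 years before decompensation and two years after it, and attributes 1.5 to 3 liver-related admissions per year to decompensated patients. At stake is whether the primary contrast measures the intervention or the case mix.

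**Working it through.** **Step 1. The two groups side by side, from the document.**

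| Feature | Intervention group | Historic cohort |
|---|---|---|
| Diagnosis | Decompensated cirrhosis (abstract) or any cirrhosis (inclusion list) | Cirrhosis |
| SPICT indicators | One general and one disease-specific | Not stated |
| Transplant-listed, or in specialised palliative care | Excluded | Not stated |
| Consent and attendance at a first visit | Required | Cannot apply |
| Start of counting | Initial study visit | No such visit; no substitute stated |
| Centres | Four departments | Same centres |

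Only the centres, and cirrhosis in the broad sense, are shared explicitly.

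**Step 2. Reproduce the plan's sample size.** Inputs from the Sample size section: reduction Δ = 2 days/year, SD = 7, 199 participants required. Alpha and power are not stated; I assume 0.05 two-sided and 80%. Equal groups follow from the similar-size wording.

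- Normal approximation: n per group = 2 × (1.960 + 0.842)² × 7² / 2² = 2 × 7.85 × 12.25 ≈ 192.3, so 193.
- Two-sample t-test version: 193.3, so 194.
- Power with 199 per group: about 0.81. Power with 199 as the total of both groups: about 0.52.

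The stated 199 is therefore close to a per-group figure, and I use it as one below.

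**Step 3. What a case-mix gap would do.** The standard error of the difference is 7 × √(2/199) = 0.70 days/year. Let b be the difference in hospital days per year that is due to case mix or start point alone. The document gives no value for b, so the range is my assumption.

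- Historic cohort sicker by b, no true effect: P(significant benefit) = Φ(b/0.70 − 1.96).
- Intervention group sicker by b, true reduction of 2 days: power = Φ((2 − b)/0.70 − 1.96).

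| b (days/year, assumed) | False benefit, no true effect | Power for a true 2-day effect, gap reversed |
|---|---|---|
| 0 | 0.025 | 0.81 |
| 0.5 | 0.11 | 0.57 |
| 1 | 0.30 | 0.30 |
| 1.5 | 0.57 | 0.11 |
| 2 | 0.81 | 0.025 |

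**Step 4. Does a larger sample help?** With 240 per group, the false-benefit probability at b = 1 and b = 2 is about 0.35 and 0.88, against 0.30 and 0.81 with 199. More patients make a biased difference more likely to reach significance.

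The calculation uses a normal approximation. Hospital days are likely to be skewed, so the figures show sensitivity and are not forecasts.

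**The case against.** The strongest reply is that this is a condensed article. Index dates and selection rules for a historic cohort, and any covariate adjustment, may sit in a full protocol or analysis plan that is not shown. That stands as far as missing detail goes, and it is why the point does not rest on the absence of an adjustment model. It does not answer two things the article does state: a start rule that the comparator cannot follow, and two population definitions that disagree.

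The SPICT disease-specific indicator may also exclude most compensated patients in practice, which would narrow the gap between abstract and inclusion list. The article does not list the indicators, so this cannot be settled here.

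A reader might infer more than the text supports:

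- **That the cohorts do start at different disease stages.** The text shows only that they can. The direction is unknown.
- **That the main comparison contains immortal time.** Counting starts at the initial visit, so survival before that visit is not credited to the intervention group. What remains is possible selection and a mismatch of index dates.
- **That an index admission inflates the comparator by a known number of days.** This would require the historic clock to start at an admission, that stay to be counted, and its length to be known. The document gives none of these, and intervention patients may also be recruited as outpatients.
- **That the 12-year and two-year medians measure the bias.** They contrast wholly compensated with wholly decompensated patients, and survival is not the primary outcome.
- **That the per-protocol analysis favours survivors.** The plan says "Both intention-to-treat (ITT) and per-protocol analyses will be conducted to assess robustness of findings" without defining the per-protocol set. Follow-up conversations are scheduled "at 6, 12, 18, 24, 30, and 36 months, or until withdrawal from the study or death", so death before a later visit need not count as a deviation.

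**Conclusion.** The concern holds in a limited form. The primary contrast sets a filtered group, counted from a study visit, against a cohort fixed only by recency, size, centres and a cirrhosis diagnosis. The trial's own population is stated inconsistently, and the named tests are unadjusted. The groups may differ in disease stage and starting point, in either direction.

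A case-mix gap as large as the 2-day target could create or cancel the whole result. A gap of half that size would raise the one-sided false-benefit probability from 0.025 to about 0.30, or cut power to about 0.30. These figures rest on the document's SD of 7, on reading 199 as per group, on a two-sided alpha of 0.05, and on gap sizes that I assumed. The document gives no evidence of how large the actual gap is. The plan should be changed, because the remedy is concrete and cheap relative to the risk.

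**What to change.** 1. Reconcile the abstract and the inclusion list into one population definition, and use it throughout.
2. Build the historic cohort by applying the same inclusion and exclusion criteria to records as far as they can be ascertained, including SPICT indicators, transplant listing, specialised palliative care and other advanced malignancy.
3. State an equivalent index date for historic patients, for example the first outpatient hepatology visit at which all criteria are met. Exclude hospital days before the index date in both groups.
4. Adjust the primary comparison for baseline severity (MELD and Child-Pugh) where it is available in both groups. The Baseline and clinical data section already plans to collect both in intervention patients. This supplements steps 2 and 3 and cannot replace them, since adjustment does not repair a different starting point.

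**Cost.** More record review, fewer qualifying historic patients and possibly a longer look-back, which weakens recency. Some SPICT indicators may be poorly documented. Consent and willingness to attend cannot be reconstructed from records, and should be reported as a residual limitation.

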### Phase 3: intervention study

A total of 240 patients and possible informal carergivers will participate in the palliative care intervention. The intervention will be initiated following completion of Phase 2, incorporating any adjustments identified during the feasibility phase.

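### Enrolling 240 patients does not cover 20% attrition from a requirement of 199: it leaves 192, because the allowance appears to have been multiplied on instead of divided out

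*Protocol article*

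**What the plan says.** The Sample size section sets out the calculation for hospital days in four steps.

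- Control value: "we assumed the historical cohort will have an average of seven days in hospital per year".
- Effect and spread: "a reduction of two days/year with an assumed SD of 7 days".
- Result: "Hence, 199 participants are required (STATA BE 18.5", with the software version in brackets.
- Allowance for loss: "With an estimated attrition rate of 20%, we aim to include 240 patients".

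The same section says that the target makes room for the attrition expected. It gives no significance level, sidedness or power, and does not say whether 199 counts one cohort or both.

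Three other sections bear on how to read it. Phase 3: intervention study places all 240 in the intervention: "A total of 240 patients and possible informal carergivers will participate in the palliative care intervention". Primary outcome describes the comparator: "compared to a recent historic cohort of a similar size from the involved centers". Statistical methods names the test for between-group comparisons: "unpaired two-sample Student’s *t*-tests will be used for normally distributed numerical data", with a rank test as the alternative.

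**The concern.** The requirement, the attrition rate and the enrolment target stand in two adjacent sentences, so they can be checked against each other without any outside assumption. They fail the check: at the plan's own attrition rate, the plan's own target does not deliver the plan's own requirement.

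This calculation supports the primary outcome. A reader who trusts the text will believe that 199 evaluable patients are secured at 20% loss. A trial team using 20% as its limit for tolerable loss would be working to a limit that the enrolment target does not support.

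**Working it through.** **Inputs.** From the Sample size section: required number 199, attrition 20%, enrolment 240, difference 2 days per year, SD 7 days. From Primary outcome: a historic cohort of comparable size. From Statistical methods: an unpaired two-sample t-test. Assumed, because the article does not state it: two-sided 5%, in line with the planned 95% confidence intervals. 80% power is assumed only where a required number is computed.

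**Step 1. Is 199 a plausible starting figure?** For two equal groups the normal approximation is n per group = 2 x (1.960 + 0.842)² x (7/2)² = 192.3, so 193. The exact calculation with the noncentral t distribution gives 194 per group at 80% power. With 199 per group, power is 81.1%, and 199 is exactly the number needed for 81%. Read as a per-cohort figure, 199 is therefore close to the expected answer and slightly on the safe side.

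**Step 2. Reproduce 240.** 199 x 1.20 = 238.8, that is 239, which rounds up to 240. This matches the target but is not the right operation. Adding 20% to the required number is not the same as losing 20% of the enrolled number.

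**Step 3. Correct inflation.** Enrolled = required / (1 - attrition) = 199 / 0.80 = 248.75, so 249. That is 9 more than 240.

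**Step 4. What 240 delivers.**

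- At 20% attrition: 240 x 0.80 = 192 evaluable, 7 below 199.
- Attrition at which 199 remain: 1 - 199/240 = 17.1%.

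**Step 5. Effect on power.** The noncentrality parameter is 2 / (7 x sqrt(1/n1 + 1/n2)), where n1 is the number of intervention patients and n2 the number of historic controls. Power comes from the noncentral t distribution, two-sided 5%.

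| Intervention | Historic cohort | Noncentrality | Power |
|---|---|---|---|
| 199 | 199 | 2.85 | 81.1% |
| 192 | 192 | 2.80 | 79.7% |
| 192 | 199 | 2.82 | 80.4% |
| 192 | 240 | 2.95 | 83.8% |

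The largest loss in the table is 81.1 - 79.7 = 1.4 percentage points.

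**The case against.** The best defence is that the slip hardly matters. The article applies attrition to the enrolled patients and says nothing of losses in the historic cohort. If that cohort supplies 199 or 240 patients, power stays above 80% even with 192 intervention patients. The primary outcome is also counted up to death or study exit, so a patient who leaves early may still contribute data. All of this stands as an argument about consequence. It does not rescue the arithmetic, because the plan itself treats attrition as a loss to be made up, and the number it gives does not make it up.

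A reader might go further and infer that 199 is itself wrong for the stated inputs. The documents do not support that. With alpha and power unstated, 199 can be neither confirmed exactly nor called an error, and as a per-cohort number it lies close to the 194 found at an assumed 80% power. Leaving alpha and power out of a condensed article is not a fault in itself.

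A reader might also notice that a one-sample calculation at a standardised effect of 0.20 (2 days with SD 10) gives 199, and conclude that this is where it came from. Nothing in the article mentions SD 10 or a one-sample or paired design, so the match is no evidence of origin.

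Finally, because 199 carries no label, a reader might take it as the total over both cohorts, which would give only 51.8% power. The article rules this out in practice: 199 is inflated to 240, all 240 receive the intervention, and the historic cohort comes on top.

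**Conclusion.** The attrition allowance is wrong as written. At 20% attrition, 240 enrolled leaves 192, not 199, and the correct inflation of 199 is 249. This rests only on figures printed in the Sample size section. That 240 came from multiplying by 1.2 is an inference from the matching number; the article does not say so.

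The practical effect is small. Under two-sided 5%, a 2-day difference and a common SD of 7, power after 20% attrition lies between 79.7% and 83.8%, depending on whether the historic cohort supplies 192 or 240 patients, against 81.1% for 199 per cohort. The point concerns a misstated figure and a missing label. It does not show that the study is materially underpowered or that 199 is a wrong requirement.

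**What to change.** Restate the sentence; enrolment can stay at 240. Either of these would do:

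- Say that 240 enrolled keeps 199 evaluable only if attrition is at most about 17%.
- Keep 20% attrition, say that it leaves 192 evaluable intervention patients, and give the resulting power with its assumptions. If the trial's own settings are two-sided 5%, a 2-day difference and SD 7, that is 79.7% against 192 historic controls, 80.4% against 199 and 83.8% against 240. The authors should confirm the significance level and the planned size of the historic cohort before printing any of these.

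In both cases label 199 as the intervention-group (per-cohort) number. If the authors prefer to keep both 199 and 20%, the target becomes 249, which means 9 more patients.

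The first two options cost only wording. The second shows power a little lower than 199 per cohort would give if the historic cohort is also 192 or 199.
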